## Research protocol summary

|                             |                                                                                                                                                                                                                                                                                                                                                                                                                                                                                                                                                                                                                                                                                                                                                                                                                                |
|-----------------------------|--------------------------------------------------------------------------------------------------------------------------------------------------------------------------------------------------------------------------------------------------------------------------------------------------------------------------------------------------------------------------------------------------------------------------------------------------------------------------------------------------------------------------------------------------------------------------------------------------------------------------------------------------------------------------------------------------------------------------------------------------------------------------------------------------------------------------------|
| Project name         | The Effects of Laryngeal Mask Airway Versus Endotracheal Tube on Atelectasis in Patients Undergoing General Anesthesia: A protocol for a prospective, randomized controlled trial                                                                                                                                                                                                                                                                                                                                                                                                                                                                                                                                                                                                                                              |
| Research objective   | The incidence of atelectasis is high in patients undergoing general anesthesia. This may further damage oxygenation and cause postoperative pulmonary complications (PPCs). The advantages of lung-protective ventilation strategy in reducing atelectasis have been confirmed; however, with the increasing application of laryngeal mask airway (LMA), there is hardly any relevant study to compare the effects of LMA and endotracheal tube (ETT) on atelectasis to date. Additionally, lung ultrasound has been increasingly used for bedside atelectasis diagnosis. For the above considerations, we designed this trial to compare the effects of LMA and ETT on atelectasis assessed using lung ultrasound scores (LUS). This study provides more powerful clinical evidence for perioperative respiratory management. |
| Design               | Prospective, Randomized, Controlled Double-blind study                                                                                                                                                                                                                                                                                                                                                                                                                                                                                                                                                                                                                                                                                                                                                                         |
| Sample size          | 180 patients                                                                                                                                                                                                                                                                                                                                                                                                                                                                                                                                                                                                                                                                                                                                                                                                                   |
| Eligibility criteria | Inclusion criteria
1. Patients $\geq 18$ years old and $< 60$ years old;
2. (ASA) physical status of I–III;
3. Patients scheduled for elective lower abdominal surgery;
4. Estimated operation time is $< 2$ h;
5. Patients and/or their authorized surrogates have signed the informed consent.                                                                                                                                                                                                                                                                                                                                                                                                                                                                                                         |
|                             | Exclusion criteria
1. Patients have difficulty with lung ultrasound, such as chest fractures, thoracic deformity, and thoracic surgical history;
2. Patients with a history of upper respiratory tract infection, smoking, general anesthesia, or mechanical ventilation in the first month before surgery;
3. Patients with cardiac insufficiency (New York Heart Association class IV), chronic renal failure (glomerular filtration rate $< 30 \text{ mL min}^{-1} \cdot 1.73 \text{ m}^{-2}$ ), liver cirrhosis (Child B or C), or pregnancy;
4. Patients with airway abnormalities or reactive airway diseases, including Mallampati classification $> \text{II}$ ;                                                                                                                                    |

|                            |                                                                                                                                                                                                                                                                                                                                                                                                                                                                                                                                                                                                                                                                                                                                                                                                                                                                                                                                                                                                           |
|----------------------------|-----------------------------------------------------------------------------------------------------------------------------------------------------------------------------------------------------------------------------------------------------------------------------------------------------------------------------------------------------------------------------------------------------------------------------------------------------------------------------------------------------------------------------------------------------------------------------------------------------------------------------------------------------------------------------------------------------------------------------------------------------------------------------------------------------------------------------------------------------------------------------------------------------------------------------------------------------------------------------------------------------------|
|                            | 
5. Patients with BMI > 30 kg/m^2;
 
6. Patients with the risk of reflux aspiration.
                                                                                                                                                                                                                                                                                                                                                                                                                                                                                                                                                                                                                                                                                                                                                                                                                                                                                              |
| Intervention        | 
Group L: In this group, LMA are selected for the artificial airway to maintain mechanical ventilation during general anesthesia. LMA size depends on the weight of the patients. After anesthesia induction and 3 min pre-oxygenation, the LMA will be inserted at the appropriate position and fixed properly.
 
Group E: In this group, ETT are selected for the artificial airway to maintain mechanical ventilation during general anesthesia. Normally, men and women choose a tube with the inner diameter (ID) = 8 mm, and 7.5 mm, respectively. Similar to Group L, ETT will be intubated with appropriate depth and fixed properly in the trachea after anesthesia induction.
                                                                                                                                                                                                                                                                                                        |
| Outcome measurement | 
Three time points were significant for outcome measurement, including 15 min after the establishment of the artificial airway (T1), the end of surgery (T2), and 30 min after extubation (T3). In addition, when patients enter the operation room (T0), they will accept the lung ultrasound assessment for the basic LUS.
 
Primary outcome: Total atelectasis LUS of 12 lung regions at T1.
 
Secondary outcomes:
 
 
1) Total atelectasis LUS of 12 lung regions at T2, T3;
 
2) Oxygenation index (PaO2/FiO2) at T1, T2, T3;
 
3) Incidence of postoperative airway complications such as hoarseness, dysphagia, and sore throat during 24 h and 48 h after surgery
 
4) The incidence of PPCs during 24 h and 48 h after surgery;
 
5) Length of stay.
 
 |
| Study duration      | 2019.2-2022.12                                                                                                                                                                                                                                                                                                                                                                                                                                                                                                                                                                                                                                                                                                                                                                                                                                                                                                                                                                                            |

## **1. Background**

For patients undergoing general anesthesia, atelectasis can occur a few minutes after pre-oxygenation and last until after surgery, further contributing to the incidence of other postoperative pulmonary complications (PPCs), increasing mortality, morbidity, and length of stay. The mechanism of atelectasis during general anesthesia has not been fully clarified, which may be related to absorption atelectasis. Airway secretion can be trapped in patients undergoing mechanical ventilation, which may block distal airway obstruction. In this situation, particularly for high  $\text{FiO}_2$ , gas inflow is blocked and gas uptake by the blood continues, which can lead to alveolar collapse and promote the formation of atelectasis.

Previous studies have demonstrated that lung-protective ventilation strategies can effectively improve atelectasis and reduce the incidence of PPCs. However, there is hardly any relevant study to compare the effects of different artificial airways on atelectasis. The endotracheal tube (ETT) has always been considered the gold standard for ensuring a patent airway and adequate ventilation during general anesthesia. The supraglottic airway device, laryngeal mask airway (LMA), is increasingly used for ventilation maintenance during general anesthesia as it is more comfortable with less irritation and lower airway resistance. In recent years, the application of LMA in surgery has become increasingly common. However, LMA cannot completely isolate the airway, and inadequate ventilation due to gas leakage could result in a low ventilation-perfusion ratio, which may lead to atelectasis. Therefore, the effects of LMA vs. ETT on atelectasis in patients undergoing general anesthesia require further investigation.

## **2. Objective**

This prospective, single-center, single-blinded, randomized controlled trial aimed to compare the effects of LMA and ETT on atelectasis in patients undergoing general anesthesia assessed by lung ultrasound and to compare the prognosis of LMA and ETT.

## **3. Study design**

### **(1) Study type**

This study is a prospective, single-center, single-blinded, randomized controlled trial. The 180 patients who meet the inclusion and exclusion criteria will be randomly allocated to the ETT and LMA groups. This trial is designed according to the updated Consolidated Standards of Reporting Trials statement and conducted at Beijing Tiantan Hospital, Capital Medical University from February 2019 to December 2022.

### **(2) Sample size calculation**

Our pre-tests estimated that the atelectasis LUS in ETT was  $8.2 \pm 3.87$ . The difference in LUS, at least for a score of 2, is considered clinically significant. The alpha level was set at 0.05, the beta value was set to 0.1, and allowing for a dropout

rate of 10%. We calculated that the total sample size required 180 patients (90 patients in each group).

### **(3) Study duration**

2019.2-2022.12

### **(4) Eligibility**

#### **Inclusion criteria**

- 1) Patients  $\geq 18$  years old and  $< 60$  years old;
- 2) American Society of Anesthesiologists (ASA) physical status of I–III;
- 3) Patients scheduled for elective lower abdominal surgery;
- 4) Estimated operation time is  $< 2$  h;
- 5) Patients and/or their authorized surrogates have signed the informed consent.

#### **Exclusion criteria**

- 1) Patients have difficulty with lung ultrasound, such as chest fractures, thoracic deformity, and thoracic surgical history;
- 2) Patients with a history of upper respiratory tract infection, smoking, general anesthesia, or mechanical ventilation in the first month before surgery;
- 3) Patients with cardiac insufficiency (New York Heart Association class IV), chronic renal failure (glomerular filtration rate  $< 30 \text{ mL min}^{-1} \cdot 1.73 \text{ m}^{-2}$ ), liver cirrhosis (Child B or C), or pregnancy;
- 4) Patients with airway abnormalities or reactive airway diseases, including Mallampati classification  $> \text{II}$ ;
- 5) Patients with  $\text{BMI} > 30 \text{ kg/m}^2$ ;
- 6) Patients with the risk of reflux aspiration.

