### (3) Lung ultrasound

Lung ultrasound assessment will be performed by a blinded trained anesthesiologist. As shown in a previous study, ultrasound scanning will select a 5–12 MHz linear transducer (SonoSite M-Turbo) to parallelly scan all the intercostal space of 12 regions from right to left, anterior to posterior of patients' chest in the supine position. The six regions are divided by anterior midline, clavicular midline, anterior axillary line, posterior axillary line, and pectoral nipple line in each hemithorax. This anesthesiologist will complete the assessment according to the LUS criteria at the same time as scanning, and the significant images and videos will be recorded.

Atelectasis LUS criteria: 0 indicates normally ventilated areas with lung sliding sign: A-line, or isolated B-lines (< 3); 1 indicates a mild reduction in lung ventilation/moderate loss of lung tissue gasification; B lines ( $\geq 3$ ) with clear boundary, regular distribution, and spacing  $\geq 7$  mm, or irregular, clear interval; 2 indicates a severe reduction in lung ventilation/severe lung tissue gasification: multiple coalescent B-lines spaced  $\leq 3$  mm and continuous fusion; 3 indicates atelectasis/pulmonary consolidation: tissue-like signs, fragment signs, and bronchial inflation signs.

[figure not shown]

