## **10. statistical analysis**

Statistical analysis will be performed using SPSS software (version 23.0; International Business Machines Inc., USA). Continuous variables will be presented as mean  $\pm$  standard deviation ( $\bar{x} \pm s$ ) media, or interquartile range, and categorical variables will be presented as numbers (proportion, %). Kolmogorov–Smirnov tests will be performed to detect the normal distribution of continuous variables. After testing for normality of continuous variables, the Student's t-test, analysis of variance, or the Mann-Whitney U-test will be used for appropriate comparisons between and within groups. Chi-squared and Fisher's exact tests will be used to analyze categorical variables. All tests will be two-tailed and conducted at a 5% significance level. Statistical significance will be set at  $P < 0.05$ . The participants missing the primary outcome will be excluded from the outcome analysis, and multiple imputations will be conducted if the unintended drop-out rates are more than 10%.

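### The exclusions name recent upper but not lower respiratory infection, and no known parenchymal lung disease, although the primary score counts B-lines and consolidation whatever their cause

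*Protocol*

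**What the plan says.** Under Exclusion criteria (section 3(4), repeated in the protocol summary), criterion 2 removes "Patients with a history of upper respiratory tract infection, smoking, general anesthesia, or mechanical ventilation in the first month before surgery". The other criteria that bear on the lung are:

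- Criterion 1 covers patients who are hard to scan; its examples are chest fracture, chest deformity and earlier thoracic surgery.
- Criterion 4 covers abnormal airways and reactive airway disease.
- Criterion 3 begins "Patients with cardiac insufficiency (New York Heart Association class IV" and also removes severe renal failure, Child B or C cirrhosis and pregnancy.

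Inclusion criterion 2 admits "American Society of Anesthesiologists (ASA) physical status of I–III".

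Section 4(3), Lung ultrasound, gives 0 to a region with fewer than three isolated B-lines, 1 to three or more separate B-lines and 2 to coalescent B-lines. For the top category it says "3 indicates atelectasis/pulmonary consolidation: tissue-like signs, fragment signs, and bronchial inflation signs". No rule on cause is given.

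Section 5 makes the total score over 12 regions at T1 the primary outcome. A T0 scan is done on arrival in the operating room. The protocol gives it no eligibility role, and section 10 names no baseline adjustment.

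**The concern.** The endpoint is meant to show atelectasis that develops under anesthesia with one airway device or the other. The score cannot tell that apart from B-lines or consolidation already present for another reason, so the eligibility list has to keep such lungs out. Criterion 2 shows that the protocol intends this, but it stops at the upper airway. Read literally, a cold three weeks before surgery excludes a patient and pneumonia three weeks before surgery does not. Known interstitial or other parenchymal disease is not named at all.

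Because the outcome is the T1 level and not the change from T0, points present on arrival count in full. At stake are the precision of the primary comparison and what a given T1 total can be taken to mean.

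**Working it through.** **Step 1. The plan's own sample size.** Section 3(2) gives SD 3.87 (ETT mean 8.2), the statement "The difference in LUS, at least for a score of 2, is considered clinically significant", 10% dropout and 90 patients per group. It also says "The alpha level was set at 0.05, the beta value was set to 0.1". Section 10 adds "All tests will be two-tailed and conducted at a 5% significance level".

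- Normal formula: n = 2(1.96 + 1.2816)² × 3.87² / 2² = 78.7, so 79 per arm. Then 79/0.9 = 87.8, so 88 per arm and 176 in total.
- t-test: 79.7, so 80 per arm. Then 80/0.9 = 88.9, so 89 per arm and 178 in total.

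The stated 180 is consistent with both. The sample size arithmetic is not in question.

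**Step 2. Planned power.** After 10% dropout, 90 × 0.9 = 81 per arm are evaluable. Two-sided t-test, 5%, difference 2, SD 3.87: power 90.5%. The margin over the 80 required is one patient per arm.

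**Step 3. Effect of unscreened lung disease.** Suppose a share p of patients, the same in both arms in expectation, carries D extra points at T1. Suppose also that 3.87 describes patients without such disease. Then

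SD′ = √(3.87² + p(1 − p)D²), with 3.87² = 14.977.

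Neither p nor D is in the protocol; the values below are assumptions.

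| p | D | p(1 − p)D² | SD′ | Power, 81 per arm |
|---|---|---|---|---|
| 0 | – | 0 | 3.87 | 90.5% |
| 1% | 4 | 0.158 | 3.89 | 90.2% |
| 1% | 8 | 0.634 | 3.95 | 89.3% |
| 2% | 4 | 0.314 | 3.91 | 89.9% |
| 2% | 8 | 1.254 | 4.03 | 88.1% |
| 3% | 6 | 1.048 | 4.00 | 88.5% |
| 5% | 8 | 3.040 | 4.24 | 84.6% |
| 10% | 8 | 5.760 | 4.55 | 79.3% |

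The normal approximation gives values 0.3 to 0.5 points higher throughout. If the pre-test patients met the same criteria, this variance is already inside 3.87 and the first row applies whatever p is.

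**Step 4. Chance imbalance.** At p = 5% and D = 8, the SD of the between-arm difference due to such patients is 8 × √(2 × 0.05 × 0.95/81) = 0.27 points, against a target of 2. Its expectation is zero under randomization.

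**Step 5. Adjusting for T0.** With a T0–T1 correlation r, the residual SD is SD × √(1 − r²). At an assumed r = 0.5 and SD 3.87 this is 3.35, and power is about 96.5%. With SD′ = 4.24 (p = 5%, D = 8) it is 3.68, and power is about 93%. The protocol gives no value for r.

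**The case against.** The case against is substantial, and most of it stands.

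- **The list is broader than colds and severe heart failure.** A reader might infer that these are all it screens out. That is not so. It also removes recent smoking, recent anesthesia or ventilation, reactive airway disease, chest surgery or deformity, GFR below 30 and Child B or C cirrhosis. The gap is specific: lower respiratory infection and parenchymal disease.
- **Not every abnormal sign scores.** Fewer than three isolated B-lines score 0. The scale has no pleural sign, so an effusion counts only through B-lines or consolidation that accompany it.
- **There is no bias between arms.** Allocation is randomized 1:1. An affected patient can also still gain points in every region below 3, so the total does not cease to respond to the airway device.
- **The size is assumed.** Patients are under 60, with elective surgery expected to last under 2 hours, so few are likely to be affected. The protocol does not say that the pre-test SD came from disease-free lungs, so the true loss could be nil.
- **T0 data exist.** Adjustment for T0 could be specified in an analysis plan that is not at hand, and it could more than restore the planned power. The absence of such a plan here is not itself the finding.

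Two further inferences are not supported. One is that old pneumonia would be counted as a new postoperative pulmonary complication: the definition lies in a cited reference that is not available. The other is that the cardiac criterion should begin at a lower class: the protocol offers no basis for a particular cut-off, and that is a clinical decision.

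What the objection does not remove is the literal gap in the list. Eligibility is fixed in the protocol, and the protocol's own criterion 2 aims at the kind of patient it then lets through.

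**Conclusion.** The point holds as a gap in the eligibility criteria with a probably small effect. Recent lower respiratory infection and known parenchymal lung disease are not excluded, while the primary outcome scores their ultrasound signs as atelectasis. The consequence is extra variance and a less specific endpoint.

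Under assumed shares of 1–2% with 4–8 extra points, power falls by 0.3 to 2.4 percentage points, from 90.5% to between 90.2% and 88.1%. A fall to about 85% needs an assumed 5% of patients with 8 extra points. A fall to about 79% needs 10%, and nothing in the protocol suggests that share. All these figures assume that the pre-test SD of 3.87 excludes such patients; if it includes them, no power is lost and only the weaker meaning of the endpoint remains.

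**What to change.** 1. In exclusion criterion 2, in section 3(4) and in the summary, write *upper or lower respiratory tract infection*.
2. Add known parenchymal lung disease to the exclusions, for example pneumonia or interstitial disease.
3. State that the T1 score will be compared between groups with adjustment for the T0 score. The T0 scan is already scheduled for every patient, so this adds no procedure. Adjustment does not replace items 1 and 2, because a region already scored 3 at T0 cannot worsen.
4. The sponsor should check whether the cardiac exclusion threshold suits an endpoint that scores B-lines. No cut-off is proposed here.

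The cost is a short amendment, a few more screen failures and a slightly narrower population. Making randomization conditional on the T0 scan is not recommended. The scan takes place on entry to the operating room, so such a rule would produce late screen failures and hold up allocation, which is out of proportion to an effect this small.
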